#### Data collection procedure

The data manager of CHU de Caen is responsible for form development, sponsor database development and data management.

Regardless of how ADR are reported, they are sent to a regional pharmacovigilance center for assessment, which includes MedDRA coding and causality analysis. Then, the regional pharmacovigilance center records the ADR in the national database.

At the end of the study, the 31 regional centers of pharmacovigilance will anonymously extract ADR reports pertaining to the first-line DMD in the trial period from the national database. The investigator’s team will identify reports of the Vigip-SEP population (of the two groups), and the Vigip-SEP investigators will compare the received date and the region, age and sex of the patient. ADR reported by patients within the 6 months of inclusion and by neurologists within the same period will be recorded in the sponsor database. Duplicates (the same ADR reports made by patients and physicians) will then be identified.

Data collected regarding the investigating centers will include the following:Type of structure: MS academic expert center, general hospital, private practice neurologistDate and result of randomizationDate of implementationRegional pharmacovigilance center attached to the investigating center

Data collected regarding patients will include the following:Socio-demographic information: patient initials, date of birth and genderConfirmation of diagnosis of RR-MS and date of diagnosisEDSS (Expanded Disability Status Scale) score at the time of inclusionDate of inclusionName and date of initiation of first-line DMD prescribedName of previous first-line DMD if the patient is not naïve of any MS treatmentIf a switch occurred in MS treatments during the course of the study, date of the current first-line DMD discontinuation and name and date of initiation of the new first-line DMDAdverse events: method of reporting, description, date, first-line DMD concerned, MedDra code, and expectedness (a previously known adverse reaction and its frequency, listed in the summary of the product characteristics of the drug)Responses to the questionnaire at 1 month (± 15 days), ADR, method of reporting, and friendliness of App (only in the experimental arm)Response to the questionnaire at 6 months (± 15 days) regarding feedback from the regional pharmacovigilance center

### Data analysis

The statistical analysis will be carried out by the Vigip-SEP scientific team.

#### Hypothesis

In the academic literature, no study has measured the impact of an App on increasing reports of ADR by patients. MedWatcher® is a user-friendly reporting App used to prepare and submit an adverse event report to the Food and Drug Administration for a hysteroscopic sterilization device. In 2012, a patient social media community adopted MedWatcher® to declare adverse reactions related to the device. On average, there were 15 times more reports via the App than via the traditional pharmacovigilance portal [19]. We assume that patient reporting will increase by 10-fold with the use of the mobile application My e-Report® over the traditional reporting method.

To follow the cluster-randomized design, the statistical unit will be the center. Therefore, the average number of ADR patient reports per patient will be pooled by center, and the comparison will be performed at the cluster (center) level. Estimation of number of centers required: this is a comparison of two means with an average for the arm standard of 20/3000 = 0.0067 or 6.7 per 1000 patients; and for the interventional arm of 200/3000 = 0.067 or 67 per 1000 patients. The power is 90% according to a bilateral test with 5% error risk and an estimated standard deviation of 0.04. Therefore, 10 centers in each arm are needed to test our hypothesis.

We will target to include 12 centers per arm to counter the trend in over-reporting due to informing physicians of the study (inflation factor). A total of 24 MS outpatient-clinic departments will recruit 180 patients (90 per arm) with the following distribution according to structure type: 10 patients per MS academic expert center, 5 patients per general hospital and 5 patients per private practice neurologist.

Statistical criteria for stopping the study: no intermediate analysis is planned, and the study will be stopped when all centers have obtained the required number of patients.

Method for accounting for missing, unused or invalid data: the patient is first informed of the study, and then, the patient’s statements are collected for 6 months. Each patient will be contacted by telephone 1 month (± 15 days) after inclusion. The 1-month follow-up questionnaire will be used to determine whether the patient should be removed from the study and replaced according to the following considerations:If the patient has reported at least one ADR, the patient data are preservedIf the patient did not report an ADR:Because they had no ADR, the patient data are preservedBecause they did not like the method of reporting, the patient data are preservedFor technical reasons (loss or breakage of the telephone/tablet), the patient is replaced by another patient, and these data are not analyzed

The sponsor CHU de Caen applies random audits of their trials of low-risk studies. The experimental intervention, defined as “Introduction to the App,” is not a risk for patients included in Vigip-SEP, and therefore, a safety monitoring board was not necessary.

There is no plan to provide access to the final data to anyone beyond the investigators.

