**Methods/design:**

We designed a multi-centric, open cluster-randomized controlled trial, called the Vigip-SEP study (NCT03029897), using the App My eReport France® to report ADR to the appropriate authorities in E2B language, in accordance with European regulations. RR-MS patients who were initiated on, or switched, first-line DMD will be included. In the experimental arm, a neurologist will introduce the patient to the App to report ADR to the appropriate French authorities. In the control arm, the patient will be informed of the existence of the App but will not be introduced to its use and will then report ADR according to the usual reporting procedures. Primary assessment criteria are defined as the average number of ADR per patient and per center. We assume that the App will increase patient reporting by 10-fold. Therefore, we will require 24 centers (12 per arm: 6 MS academic expert centers, 3 general hospitals, 3 private practice neurologists), allowing for an expected enrollment of 180 patients (alpha risk 5%, power 90% and standard deviation 4%).

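### The stated 90% power uses a standard deviation of 0.04 that centres of 5 and 10 patients do not give; at the plan's own rates, 12 centres per arm have about 50% power

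*Protocol article*

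**What the plan says.** The Hypothesis section of the protocol article fixes the analysis at centre level: "the average number of ADR patient reports per patient will be pooled by center, and the comparison will be performed at the cluster (center) level". The control mean is given as follows: "this is a comparison of two means with an average for the arm standard of 20/3000 = 0.0067 or 6.7 per 1000 patients". The App-arm figure is given "for the interventional arm of 200/3000 = 0.067 or 67 per 1000 patients". The precision claim is: "The power is 90% according to a bilateral test with 5% error risk and an estimated standard deviation of 0.04". From this comes the statement "Therefore, 10 centers in each arm are needed to test our hypothesis". The abstract repeats the same inputs ("alpha risk 5%, power 90% and standard deviation 4" per cent).

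The target is then raised to 12 per arm for a different reason: "We will target to include 12 centers per arm to counter the trend in over-reporting due to informing physicians of the study (inflation factor").

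Planned recruitment is "10 patients per MS academic expert center, 5 patients per general hospital and 5 patients per private practice neurologist". The abstract gives the mix per arm as six academic centres, three general hospitals and three private practices. That is six centres of 10 patients and six of 5, or 90 patients per arm. The Primary outcomes section defines each centre's value as its number of reports divided by its number of patients.

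**The concern.** The sample size is counted in centres, so 0.04 can only be the SD of centre means. The calculation makes no use of centre size, although a rate measured on 5 or 10 patients is mostly counting noise. A 10-patient centre can record only 0, 0.1, 0.2 and so on; a 5-patient centre only 0, 0.2, 0.4 and so on. With an App-arm mean of 0.067, most centres will record zero or one report, and a single report moves a centre's value by 0.1 or 0.2. An SD of 0.04 looks too small for such data.

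If so, the trial could easily miss the 10-fold increase it was designed to find. Readers told that power is 90% could then take a non-significant result as evidence that introducing patients to the App does not work.

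**Working it through.** **Inputs (protocol article).** Rates 20/3000 = 0.00667 and 200/3000 = 0.0667, difference 0.06; SD 0.04; two-sided 5%; power 90% (Hypothesis). Six centres of 10 and six of 5 patients per arm (abstract and Hypothesis). Centre value = reports/patients (Primary outcomes). Test: Student's t or Wilcoxon on centre means, weighted by centre size (Statistical analysis plan section).

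**1. Reproduce the plan.** n = 2 × (1.960 + 1.282)² × (0.04/0.06)² = 9.3, rounded up to 10 per arm. With SD 0.04, 12 per arm would give 94% (noncentral t) to 96% (normal approximation). The arithmetic is right given the SD.

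**2. SD implied by the planned centre sizes.** Assume Poisson counts and no true variation between centres. The variance of a centre mean is rate/m. Averaged over half the centres at m = 10 and half at m = 5, this is rate × (0.1 + 0.2)/2 = rate × 0.15.

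- App arm: 0.0667 × 0.15 = 0.0100, SD 0.100.
- Control arm: 0.00667 × 0.15 = 0.0010, SD 0.032.
- Pooled: √((0.0100 + 0.0010)/2) = √0.0055 = 0.074.

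A binomial model (at most one report per patient) gives 0.072.

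**3. Lower bound without the Poisson model.** Take the least variable distribution on the attainable values that keeps the planned arm means.

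- App arm: every 10-patient centre has exactly one report (mean 0.1, variance 0). The 5-patient centres average 0.033, with one report in a sixth of them: variance 0.2² × (1/6) × (5/6) = 0.00556. Total variance = 0.00556/2 + ((0.1 − 0.033)/2)² = 0.00389, SD 0.062.
- Control arm: all reports fall in 10-patient centres (mean 0.0133, variance 0.1² × 0.133 × 0.867 = 0.00116). Total variance = 0.00116/2 + (0.0133/2)² = 0.00062, SD 0.025.
- Pooled: √((0.00389 + 0.00062)/2) = 0.047.

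If both centre sizes share the arm's rate, as the plan implies, the same argument gives a pooled minimum of 0.057.

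**4. Power at 12 centres per arm for 0.0067 against 0.067.**

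| Assumption | Method | Power |
|---|---|---|
| SD 0.04 (plan) | noncentral t | 94% |
| SD 0.047 (lower bound) | noncentral t | 84% |
| SD 0.057 (lower bound, common rates) | noncentral t | 69% |
| SD 0.074 (Poisson) | noncentral t | 47% |
| Poisson | simulation, Student's t | 50% |
| Poisson | simulation, size-weighted t | 54% |
| Poisson | simulation, Wilcoxon | 52% |
| Poisson, between-centre CV 0.5 (assumed) | simulation, Student's t | 45% |
| Poisson, between-centre CV 1.0 (assumed) | simulation, Student's t | 33% |

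The t-test simulations used 40,000 trials and the Wilcoxon 8,000. The binomial model raises the three simulated figures without between-centre variation to 53%, 57% and 55%.

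**5. What the design can detect.** Keep 12 centres per arm and the control rate at 0.0067. Simulated power is 86% (Student's t) and 90% (size-weighted t) at an App-arm rate of 0.12, and 90% and 92% at 0.13. These rates are 0.12/0.00667 = 18-fold and 0.13/0.00667 = 19.5-fold. The equal-variance t formula is more pessimistic and needs about 0.163 (24-fold).

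**6. Scale of the data.** Expected reports are 90 × 0.0667 = 6.0 in the App arm and 90 × 0.00667 = 0.6 in the control arm. The chance of no control report at all is exp(−0.6) = 55%.

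For orientation, with this mix of centre sizes 2 × 10.51 × (0.0742/0.06)² = 32.1, so 33 centres per arm, would be needed by the normal formula. Simulated Student's t power reaches 90% at about 28.

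**The case against.** **The low power depends on a model that the plan does not state.** The distribution-free bound alone lowers power only from 94% to 84%; the fall to about 50% needs Poisson or binomial counting. This is fair. But the bound requires every 10-patient App centre to record exactly one report, which nothing in the plan supports. Independent counting is the ordinary model, and it is favourable here because it leaves out centre effects and repeated reports by one patient. The implied SD is also an expected value: about 4% of simulated trials showed an observed pooled SD of 0.04 or less, typically those with very few reports.

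**The rates may be higher in the trial.** The Strengths and limitations section expects over-reporting, and patients are telephoned at 1 month. If both rates doubled (assumption), simulated Student's t power would be about 83%. If over-reporting added equally to both arms, say 0.04 against 0.10 (assumption), it would be about 27%. True power is therefore uncertain in both directions. The 90%, however, is claimed for 0.0067 against 0.067, and there it is wrong.

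**The SD may be derived in the full protocol.** An article need not show this, and its absence is not part of the point. Any derivation would still have to fit the printed rates and centre sizes.

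**The extra centres and the hierarchical model.** All power figures above already use 12 centres, and the added two are assigned to over-reporting. The patient-level model is planned in addition; the 90% refers to the centre-level comparison of two means.

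**Conclusion.** The concern holds. The number of centres follows from the stated inputs, but the SD of 0.04 is incompatible with the article's own rates and centre sizes. It lies below even the smallest pooled SD that the attainable values allow (0.047) and is about half the 0.074 expected from counting variation. Power for the assumed 10-fold effect at 12 centres per arm is about 50%, some 40 percentage points below the claim, whichever planned test is used.

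This rests on the plan's own rates, independent Poisson reports and no variation between centres. Centre effects or clustering of reports within patients would lower it. The rates are also annual national figures applied to a 6-month window, and a lower 6-month rate would lower it too. Higher rates at the same 10-fold ratio would raise it.

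**What to change.** In the Hypothesis section and the abstract, replace the SD of 0.04 with the value implied by the planned centre sizes, and restate the power with the method named. For example:

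> With six centres of 10 patients and six of 5 per arm, counting variation alone gives a pooled SD of centre means of at least 0.074. Power to detect 0.0067 against 0.067 reports per patient is about 50% (simulated t test, Poisson counts, no between-centre variation). The App-arm rate detectable with 90% power is about 0.12 (size-weighted t) to 0.13 (unweighted t). A non-significant result is inconclusive about a 10-fold increase.

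The detectable rate should be labelled as simulated, because the t formula gives about 0.163.

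The cost is a few sentences and a less favourable stated power. No change to enrolment, centres or planned tests is requested.

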## Methods/design

### Aim, design and setting

The overall aim of our Vigip-SEP trial is to study reporting of ADR by RR-MS patients using a mobile application.

The first aim is to evaluate the increase in ADR reporting by mobile application use. The second aim is to evaluate the quality of patient reporting. We will also evaluate the effect of patient involvement in pharmacovigilance on physician reporting (boost effect). Additionally, the user-friendliness of the application will be assessed according to the patients’ satisfaction, the patients’ judgment of practicability, and the patients’ suggestions for improvements.

The designed study is a multi-centric, open cluster-randomized controlled trial.

The Vigip-SEP study is set in France. The trial sponsor is CHU de Caen, an academic hospital, responsible for protocol decisions and quality control. Coordination is provided by an investigative team of MS academic experts at the center of CHU de Caen.

This study was approved by the Ethics Committee of Nord-Ouest III with approval number 2016–42. The privacy of the participants and their personal medical records will be guaranteed by treating the data according to the French law n. 78–17 of 6 January 1978 and the “European Union Data Protection Directive (95/46/EC 24 October 1995).”

The approved version of Vigip-SEP is V3 29.11.2016; the recruitment began in June 2017, and the end date is anticipated in May 2018.

The sponsor CHU de Caen is responsible for reporting any protocol modifications to the centers, ethic committees and ANSM.

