**Fig. 1 Fig1:**
[figure not shown]
Enrollment, interventions and assessments in the Vigip-SEP study

Centers will be stratified based on structure type then randomly allocated (1:1) to the experimental arm (these centers will introduce all patients to use of the App) or to the control arm (these centers will not introduce patients to use of the App). Centers will be informed of the randomization the day of the trial initiation visit.

Clustering avoids a “contamination” bias (in the epidemiological sense) of different patients followed by the same prescriber.

Neurologists will successively include all patients meeting the criteria until they have reached the number of subjects to be included. In 1 year, MS academic expert centers are expected to include 10 patients, and general hospitals and private practice neurologists are expected to include 5 patients. Neurologists will inform patients about the Vigip-SEP study and obtain the patients’ written informed consent.

CHU de Caen conforms to National Informatic and Liberty French Law and, therefore, patient confidentiality will be protected.

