### Outcome measurements

#### Primary outcomes

The primary outcome is the number of ADR patient reports. ADR reports will be collected in both arms for 6 months after the inclusion of each patient from the national database of French authority, ANSM (see “Data collection procedure” below).

An example of the method of aggregation is as follows. For center 1, *m*1 = *n*1 reports/*N*1 patients, where *n*1 is the number of ADR in the center, and *N*1 is the number of patients included in the center.

The method of aggregation in each group follows the formula Ʃ*mx*/*N*, where *N* is the number of centers in the group.

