## Discussion

Application use by patients could be an integral part of the pharmacovigilance system that is in place in France. This study aims to improve the efficiency of the pharmacovigilance system by increasing the number of reports and, therefore, allowing earlier detection of events to prevent and minimize risks.

The robust methodology, with a clustered randomized national study, will determine the usefulness of national support for reporting by mobile application.

The results of this study should be available in the summer of 2018, and we hope that these results will be consistent with our assumption that (1) the efficiency of the post-marketing authorization system will be improved by an increase in reporting of ADR via the mobile application and (2) the therapeutic safety of MS patients will be improved by a better knowledge of the safety profile of DMD.

Developing a culture of reporting ADR by RR-MS patients is a relevant goal. In 2015, in France, 20 ADR were reported by MS patients compared with 271 ADR reported by physicians concerning first-line DMD according to data from the French National Database of Pharmacovigilance. In the future, we hope that this new method of reporting will improve pharmacovigilance by RR-MS patients and can be extended to include all new DMD. The overall goal is to be able to improve the early detection of unexpected adverse reactions not revealed by clinical consultations. If our hypothesis is confirmed, other neurological diseases could be explored using this method.

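### The stopping rule, extraction point, one-year recruitment and summer 2018 results date cannot all stand with a 6-month outcome window for every patient

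*Protocol article*

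**What the plan says.** All statements are in the protocol article. One group sets the outcome window:

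- Primary outcomes: "ADR reports will be collected in both arms for 6 months after the inclusion of each patient".
- Data collection procedure: "ADR reported by patients within the 6 months of inclusion and by neurologists within the same period will be recorded in the sponsor database". The same section lists "Response to the questionnaire at 6 months (± 15 days) regarding feedback from the regional pharmacovigilance center".
- The missing-data paragraph under Data analysis repeats that patients' "statements are collected for 6 months".

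A second group sets the calendar and the close:

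- Aim, design and setting: "the recruitment began in June 2017, and the end date is anticipated in May 2018".
- Randomization: "In 1 year, MS academic expert centers are expected to include 10 patients", with 5 each for general hospitals and private neurologists.
- Hypothesis, on stopping: "the study will be stopped when all centers have obtained the required number of patients".
- Data collection procedure: the 31 regional centres extract reports when the study ends, for a trial period that is not defined. Each report must first be assessed and coded regionally and entered in the national database.
- Discussion: "The results of this study should be available in the summer of 2018".

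Under Primary outcomes, the centre mean is reports divided by patients included. Time observed does not enter it.

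**The concern.** Taken at its word, the stopping rule closes the study on the day the slowest centre fills its quota, and extraction is tied to that close. Anyone included in the preceding 6 months would then have an incomplete window. Reports that such a patient makes after the cut are lost, while the patient still adds one to the denominator, so the centre mean is pulled down. Regional processing before database entry adds a lag, so some reports made in time could also be missed.

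The endpoint has little to spare. On the plan's own rates, 90 patients per arm give about 90 × 0.067 = 6.0 reports in the App arm and 90 × 0.0067 = 0.6 in the control arm.

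**Working it through.** **1. The plan's own figure.** Inputs from the Hypothesis section: means 20/3000 = 0.0067 and 200/3000 = 0.067, difference 0.060, SD 0.04 between centres, two-sided 5%, power 90%.

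n per arm = 2 × [0.04 × (1.960 + 1.282) / 0.060]² = 9.34, rounded up to 10. This agrees with the plan. Power is 91.8% (normal) or 88.7% (noncentral t) with 10 centres per arm, and 95.7% or 93.9% with the targeted 12. Patients: 2 × (6×10 + 3×5 + 3×5) = 180, as stated.

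**2. The calendar.** Take the start of June 2017 as month 0. One year of recruitment ends at month 12 (end of May 2018). The last 6-month window ends at 12 + 6 = month 18 (about November 2018), or 18.5 with the 15-day tolerance on the 6-month call. Summer 2018 is at most about month 15.

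The May 2018 date can be read in two ways:

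- As the end of recruitment: the last windows close about November 2018, after the announced results.
- As the end of the study: full windows require the last inclusion by about November 2017 (12 − 6 = month 6), against the stated year of recruitment.

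Neither reading reconciles all the statements.

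**3. Follow-up if data close early.** The article gives no accrual curve, so uniform entry over 12 months is assumed. With entry at month u and close at month C, observed time is min(6, C − u). The share with a full window is (C − 6)/12.

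| Close | Full 6 months | Mean observed time |
|---|---|---|
| Month 12 | 50% (about 90 of 180) | 0.5×6 + 0.5×3 = 4.5 |
| Month 14 | 67% | 0.667×6 + 0.333×4 = 5.3 |
| Month 15 | 75% | 0.75×6 + 0.25×4.5 = 5.6 |
| Month 18 | 100% | 6 |

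**4. Effect on power, month-12 close.** If reports are spread evenly over the 6 months, the fraction kept is 4.5/6 = 0.75. Expected reports fall to about 4.5 and 0.45 per arm, and the difference to 0.060 × 0.75 = 0.045. Holding the SD at 0.04, with 12 centres per arm:

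- Standard error = 0.04 × √(2/12) = 0.0163.
- 0.045/0.0163 − 1.960 = 0.80, so power is 79% (normal); noncentral t gives 75%.
- For 90% power, n = 2 × [0.04 × 3.242 / 0.045]² = 16.6, so 17 centres per arm.

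If reports come early (exponential reporting times with assumed means of 1 to 3 months), 83% to 92% of reports are kept. Power with 12 centres per arm is then 86% to 92% (normal) or 83% to 90% (t).

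**5. Effect on the ratio.** With equal accrual timing, both arm means are multiplied by the same factor, so the assumed 10-fold ratio is unchanged. The loss is in the absolute difference and in power.

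**The case against.** The best defence is that nothing in the article orders follow-up to be cut. The 6-month window is set out repeatedly and a 6-month call is planned. The stopping sentence sits beside the statement that there is no interim analysis, and can be taken to mean that enrolment ends when quotas are met. The May 2018 sentence has recruitment as its subject and fits the one-year accrual. On that reading extraction follows the last window, and only the forecast in the Discussion is wrong.

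Much of this stands. It rules out several stronger conclusions that a reader might draw:

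- That late patients cannot have their window, or that the centre means are truncated by design. Truncation is only one possible result of the conflict.
- That patients cut short count as complete non-reporters. Reports made before the cut stay in the numerator; only later ones are lost.
- That the arms would be biased against each other. This needs different accrual timing by arm. Nothing in the article indicates it, and every centre has a fixed quota.
- That the centre rates need a patient-month denominator. Once windows are complete it is unnecessary, and it would depart from the reports-per-patient outcome on which the sample size rests.

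The defence does not remove the conflict. Even on its reading the results date is incompatible with a full window for everyone, and the stopping sentence still names the study, not recruitment, as what stops.

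**Conclusion.** The conflict is real: about 18 months are needed, against 12 to the stated end date and at most about 15 to the announced results. The harm is conditional. It arises only if the stopping and extraction wording, or the results date, is allowed to override the 6-month window.

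The drop in power to about 75-79% is the adverse end of a range. It rests on uniform accrual, a close exactly at last inclusion, evenly spread reports and an unchanged SD. Early reporting or a later close makes it smaller. Because the extraction rule determines which reports are counted in the primary outcome, the wording should be settled before any extraction.

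**What to change.** Reconcile the stopping, extraction and calendar statements with the 6-month window:

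1. In the Hypothesis section, state that recruitment, not the study, stops when all centres have reached their numbers.
2. State that the study ends, and the national database is extracted, only after the last included patient's 6-month window plus a fixed allowance for regional assessment and entry.
3. In Aim, design and setting, make clear that May 2018 is the anticipated end of recruitment.
4. Correct the summer 2018 results date in the Discussion.

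The primary outcome and its denominator stay as they are. The cost is a few sentences of wording and results about 6 months later.

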### Strengths and limitations

This study has several strengths. First, the design, a randomized control trial, will allow a causal interpretation in terms of outcomes. In addition, including several types of centers (academic expert centers, general hospitals and private practice neurologists) will increase the external validity of the results. Furthermore, the study is focused on the use of an innovative tool, a mobile application, by a population in real-life conditions.

We are also aware of several potential limitations. This is an open trial and, therefore, over-reporting due to informing the patients and physicians is expected and cannot be neutralized. Moreover, patients failing to report ADR by the App may have had a technical problem or may have forgotten to report the ADR. Indeed, the user-friendliness of the mobile application has not been tested. To counter this limitation, 1 month after inclusion, we will ensure by a telephone call that patients report all ADR and are able to use the mobile application effectively. Feedback from regional pharmacovigilance centers will also be investigated by a telephone call at 6 months after inclusion to explore patient satisfaction [16].

Currently, patients describe ADR via the App via free verbatim that is later coded by pharmacologists of pharmacovigilance centers using the MedDra dictionary. Encouraging this reporting requires the accompaniment of regional pharmacovigilance centers. In addition, informing patients, as proposed in the study, requires time by neurologists. Financial resources should be put in place for this support, which could be included, for example, in a patient education program.

Pharmacovigilance is a major public health issue. First-line DMD, whose risk profiles are not fully known, that have been newly released to the market must be carefully monitored. Patient involvement in the pharmacovigilance system is already accepted to be a valuable asset but must be further developed. RR-MS patients, who are already well-adapted to managing their disease, could be key players in effective pharmacovigilance. In a second phase, we plan to develop applications specifically dedicated to new DMD.

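### Included patients who have not reported by about 1 month because their device was lost or broken are removed and replaced: an outcome-dependent, post-allocation exclusion that conflicts with the stated denominator and probably favours the App modestly

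*Protocol article*

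**What the plan says.** The rule is in the Protocol article, Data analysis, under *Hypothesis*, in the paragraph on missing, unused or invalid data. Each patient is telephoned at 1 month (± 15 days), and the answers decide who stays:

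- Reported at least one ADR: kept, with no condition on the device.
- Not reported because there was no ADR: kept.
- Not reported because the patient disliked the method: kept.
- Not reported for device reasons: "technical reasons (loss or breakage of the telephone/tablet), the patient is replaced by another patient, and these data are not analyzed".

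The *Primary outcomes* section defines each center's result as its number of reports divided by the number of patients included there. Reports are taken from the national database for 6 months after each inclusion, in both arms.

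The *Control arm* section gives control patients the 1-month questionnaire too. The *Strengths and limitations* section calls the trial open and accepts that "patients failing to report ADR by the App may have had a technical problem".

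**The concern.** Two patients with the same broken telephone are treated differently according to whether they have already reported, and reporting is the primary outcome. The decision comes after the center's allocation is known and inside the 6-month outcome window.

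The paragraph presents this as handling of missing or invalid data, but a lost device does not make the outcome missing. Reports are extracted from the national database whatever became of the device, so a patient without a report has an observed count of zero. The intervention, which the same section defines as being introduced to the App, has also already been delivered by the time the telephone breaks.

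At stake is the comparison of all included patients as allocated. Removing patients with zero reports and recruiting others in their place tends to raise a center's mean. If this happens more often in App centers, the App effect is overstated.

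**Working it through.** **The plan's own figure.** Inputs from *Hypothesis*: control mean "an average for the arm standard of 20/3000 = 0.0067 or 6.7 per 1000 patients"; App mean "for the interventional arm of 200/3000 = 0.067 or 67 per 1000 patients"; and "The power is 90% according to a bilateral test with 5% error risk and an estimated standard deviation of 0.04". The difference is 200/3000 − 20/3000 = 0.0600.

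Centers per arm = 2 × [0.04 × (1.960 + 1.282) / 0.06]² = 9.34, rounded up to 10. This agrees with "10 centers in each arm are needed to test our hypothesis" (12 are planned). The point below does not alter that number.

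**The two passages side by side.** *Primary outcomes* divides by the patients included in the center. The replacement rule takes some included patients out of that number and puts others in. Both cannot hold.

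**Where the rule acts.** The wording covers each patient, and controls also receive the 1-month call. App-arm patients are taught to report on the device (*Intervention arm*). Controls use the usual procedures (*Control arm*), which the *Background* lists as a form on the agency's website, or contact with a regional center electronically or by telephone. Device loss is therefore a likelier reason for not reporting in the App arm. This is an inference from the reporting routes and is not stated in the document.

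**Size.** Let M be the 6-month mean over all App-arm patients originally included, q the share removed, and r the mean 6-month count that the removed patients would have had. If replacements report like those retained, the analysed mean is

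A = (M − q·r) / (1 − q).

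With r = 0 this is M/(1 − q), the largest possible inflation for a given q. The documents give no q, so the values below are assumptions. M = 0.0667 and the control mean is 0.0067.

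| q in App arm | Patients of 90 | Factor | Analysed App mean | Difference (plan 0.0600) | Ratio, no controls removed (plan 10) | Ratio, controls removed at q/2 |
|---|---|---|---|---|---|---|
| 1% | 0.9 | 1.01 | 0.0673 | 0.0607 | 10.1 | 10.05 |
| 5% | 4.5 | 1.05 | 0.0702 | 0.0635 | 10.5 | 10.26 |
| 10% | 9 | 1.11 | 0.0741 | 0.0674 | 11.1 | 10.56 |

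If removal were equally common in both arms, the ratio would stay at 10, but the difference would still be inflated: 0.0600/0.95 = 0.0632 at 5%.

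**Direction.** A exceeds M only if r < M. With q = 5% and an assumed r = 0.10, A = (0.0667 − 0.0050)/0.95 = 0.0649, which is 2.6% below M. The bias can therefore reverse.

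**Could it create a finding?** With 12 centers per arm and the planned SD, the standard error is 0.04 × √(2/12) = 0.0163. Suppose there is no true effect, both means are 0.0067, and 10% are removed in the App arm only. The spurious difference is 0.0067 × (1/0.90 − 1) = 0.00074, or 0.00074/0.0163 = 0.05 standard errors. If both arms reported at 0.0667, it would be 0.0074, or 0.45 standard errors. Neither approaches significance.

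**Granularity.** The plan expects 90 × 0.0667 = 6 reports in the App arm and 90 × 0.0067 = 0.6 in the control arm. In a 5-patient center, one replacement changes a fifth of the denominator.

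**The case against.** The best defence is that the rule is prespecified, narrow and not confined to one arm. It covers physical loss or breakage only. Patients who dislike the method stay in, and software faults are not named as grounds for removal, so much of what reflects the App's own performance is retained. Every patient in both arms must have a device able to host the App, controls are told that it exists, and some usual routes also need a device. The number removed may be one or two.

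All of that stands, and it limits the claim. Three stronger readings are tempting, and the documents do not support them:

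- **That only the App arm loses patients.** The rule applies to every patient, and controls are also called at 1 month. Only a difference in frequency can be inferred.
- **That the bias can run only towards the App.** Non-reporters without an ADR are kept, so those removed are essentially patients who had an ADR and had not reported it. About 5 months remain in which they might report by a new device or another route, and their 6-month mean could exceed 0.067.
- **That the rule could produce a positive trial.** The arithmetic above shows that it would not by itself do so, and the planned contrast is 10-fold.

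Two smaller cautions apply. The remark about technical problems in *Strengths and limitations* is a listed limitation; it does not define device loss as part of App performance. The database outcome is also not perfectly known for each patient, because anonymous reports are matched on received date, region, age and sex. That matching does not depend on the patient's device, so it gives no reason to exclude these patients.

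What the defence does not answer is that removal depends on the outcome so far, happens after allocation, and contradicts the stated denominator.

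**Conclusion.** The point holds as a defect in a stated rule. Patients are removed after allocation according to their primary outcome to date, in an open trial, against a denominator defined as all patients included in the center.

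The expected direction is towards the App. This rests on two assumptions: that removal is more common in the App arm, and that removed patients would have reported less over 6 months than their replacements. The size cannot be derived from the documents. As an upper bound, with no reports from removed patients, the App-arm mean is inflated by a factor of 1.01, 1.05 or 1.11 at assumed removal shares of 1%, 5% or 10%. That is small beside the planned 10-fold increase and would not by itself create a significant result. Prespecifying the rule makes it transparent but does not remove the dependence on the outcome.

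**What to change.** Delete the replacement rule from the primary analysis. Keep every included patient in the center's N, in the arm to which the center was allocated, and count that patient's reports from the national database to 6 months whatever happened to the device. Describe device loss and breakage by arm, as recorded at the 1-month call. If the sponsor wants the present exclusion, retain it only as a labelled sensitivity analysis.

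The cost is one paragraph of the protocol. No new data are needed, since the database extraction already covers these patients, and the requirement of 10 centers per arm (12 planned) is unchanged. The downside is a possibly slightly lower App-arm mean.
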